#### 8.3.4. Illness Related to the Study

(1)Definition of illness

Disease, disability, death, infectious disease, or abnormal laboratory test values and symptoms suspected to be caused by the implementation of the study are defined as illnesses. Moreover, a causal relationship between the study drug used and the study procedure will be determined by the principal investigator and co-investigator.

(2)Predictability

Events that cannot be predicted from the package insert (container/encapsulation) of the study drug and the precautions written in the interview form are categorized as “unknown,” whereas those that are listed and can be predicted are categorized as “known”.

(3)Causality

In this study, causality is defined as a causal relationship that cannot be denied, based on the judgement of the principal investigator and co-investigator. When deciding, they will consider not only the temporal relationship with the initiation of interventional but also the course of underlying diseases, complications, concomitant medications, study procedures, accidents, and other environmental factors. Causality is judged and recorded throughout the study period.

#### 8.3.5. Subjects and Reporting Period for Reporting Illness

If the investigator becomes aware of a disease or other matters that requires reporting within the time limit listed in the table below, the principal investigator reports it to the administrator of the medical institution and an accredited clinical research review board within the specified period. Additionally, this information will be provided to manufacturers and distributors of pharmaceuticals (Table 2).

#### 8.3.6. Procedures for Reporting Illnesses: Procedures in the Event of Illness

(1)Co-investigators report the event to the principal investigator if they become aware of the illness. The principal investigator and co-investigators will then take appropriate measures for the study subject, take the best care, and record it in the medical records.(2)If the illness is subject to reporting within the deadlines listed in Table 1, the investigators must submit a report to the accredited clinical research review board within the specified reporting deadline.

#### 8.3.7. Procedures for Reporting Illnesses: Procedures of Regular Reporting

(1)The principal investigator will use the jRCT system to report the number of illnesses to the Minister of Health, Labor, and Welfare.(2)The principal investigator will report the number of illnesses to the administrator of the medical institution and to the accredited clinical research review board within the period specified in Table 1.(3)With the approval of the accredited clinical research review committee, the principal investigator will use the jRCT system to report to the Regional Bureau of Health and Welfare within the period specified in Table 1.

#### 8.3.8. Observation of Research Subjects After Occurrence of Adverse Events

Follow-up surveys of the study subjects after the occurrence of adverse events will be conducted until resolution of adverse events or until the principal investigator or co-investigator determines that follow-up surveys are unnecessary.

### 8.4. Frequency and Plans for Auditing Trial Conduct

Audits will be conducted as necessary in accordance with the regulations of the Clinical Research Act.

### 8.5. Plans for Communicating Important Protocol Amendments to Relevant Parties (E.G., Trial Participants, Ethical Committees)

(1)When amending the study protocol and informed consent form, the principal investigator must obtain a review from an accredited clinical research review committee prior to the amendment and report the details to the administrator of the implementing medical institution. In the case of changes related to the implementation system or other significant changes, approval from the administrator of the implementing medical institution should be obtained, as necessary. The principal investigator or co-investigator must not conduct the study using a modified research protocol or informed consent form before obtaining approval from the committee or the administrator of the implementing medical institution.(2)When changes in the study protocol involve changes in the implementation plan, the principal investigator must submit a notification of changes to the Minister of Health, Labor, and Welfare after obtaining approval from the accredited clinical research review committee. The principal investigator or co-investigators must not conduct the study using the modified study protocol and informed consent form before submitting the notification of modification to the Minister of Health, Labor, and Welfare, and before such modification is published in the jRCT.

### 8.6. Dissemination Plans

Communicating the trial results to participants, healthcare professionals, and the public will be done through domestic and international conference presentations and publications.

## 9. Discussion

This study aims to investigate the immune response to the recombinant zoster vaccine Shingrix^®^ in Japanese patients with RA receiving MTX + upadacitinib combination therapy, MTX monotherapy, and upadacitinib monotherapy. To the best of our knowledge, this is the only prospective study conducted in Japan examining the efficacy and safety of this vaccine in this cohort. This study could provide pivotal evidence in Japan, where the incidence of herpes zoster is relatively higher. Compared to a previous US study of this vaccine in the same population [21], the present study’s parallel triple-arm design offers an advantage in presenting validated results.

Another strength of this study is that it examines both humoral (e.g., anti-gE, VZV-specific antibodies) and cellular (e.g., gE-specific CD4+ T-cells) immunity, since cellular immunity is considered a more reliable predictor of herpes zoster protection [12,13,14]. Furthermore, ancillary RNA sequencing will be performed using PBMCs, allowing the analysis of gene expression before and after vaccination. Such a comprehensive approach will allow for a multifaceted examination of vaccine immunogenicity. If these studies prove the efficacy and safety of the vaccine, it will provide beneficial insights into herpes zoster prevention strategies for patients receiving JAK inhibitors, not only in Japan but also in other countries.

Despite the insights offered in our study, several limitations should be acknowledged. First, this is a single-center prospective study that will only enroll Japanese patients with RA. Therefore, the results cannot be generalized globally. Second, due to the study’s exploratory design, the sample size is relatively small (target of 23 patients per group) in consideration to feasibility. Third, the primary endpoint in this study was set at 4 weeks after the second Shingrix^®^ dose, which was based on a previous study [11]. However, other studies have evaluated the immunogenicity of the vaccine up to 10 years [22,23]. Thus, this study only evaluates the short-term immunogenicity of the vaccine. Lastly, we will not examine the incidence of herpes zoster due to the short observation period. To verify the effectiveness of the vaccine, further studies must include a larger number of patients with longer-term observations [6,24].

Nevertheless, this study will provide critical evidence on Shingrix^®^ effectiveness and tolerability in Japanese patients with RA receiving upadacitinib, which is particularly relevant given the nation’s high incidence of herpes zoster. Until recently, the recombinant zoster vaccine has been limited to individuals aged 50 years and over; however, individuals aged 18 years and over who are considered to be at high risk of herpes zoster have been eligible for vaccination in Japan since June 2023. Furthermore, upadacitinib has been indicated for other diseases that develop at a relatively young age, including ankylosing spondylitis, atopic dermatitis, ulcerative colitis, non-radiographic axial spondyloarthritis, and Crohn’s disease. As such, the study provides useful evidence for these cohorts.

## 10. Trial Status

The date the protocol was approved: 29 September 2022 (version 1.0).

The date recruitment began: 14 October 2022.

The date first patient registered: 26 December 2022.

The date the protocol was revised: 26 Oct 2023 (version 2.3).

The date the revised protocol was approved: 28 November 2023.

Trial status: Recruiting.

The approximate date when recruitment will be completed: 31 October 2024.

The observation period: From 12 October 2022 to 31 March 2025.

The estimated date for study completion: 31 March 2026.

## Figures and Tables

**Figure 1 jcm-13-07321-f001:**
[figure not shown]
Overview of the study.

**Figure 2 jcm-13-07321-f002:**
[figure not shown]
Sample size explanation. IC: informed consent, MTX: methotrexate, RA: rheumatoid arthritis, UPA: upadacitinib.

**Table 1 jcm-13-07321-t001:** Participant timeline.

	Before Enrollment	At Enrollment	Week 4	Week 8	Week 12	Week 20
Visit	0	1	2	3	4	5
Allowance			+1 week	+2 week	+3 week * 1	−2~+4 week * 2
Informed consent		X				
Eligibility screen		X				
Shingrix^®^ injection		X		X		
Disease activity of RA	X	X	X	X	X	X
Assessment of adverse events		X	X	X	X	X
Blood tests * 3 Urine tests * 4 Serum storage	X	X	X	X	X	X
Immunogenicity * 5		X	X		X	
Additional blood collection		X	X		X	
Confirmation of concomitant drug	X	X	X	X	X	X
RA flare						X

* 1: 4 weeks + 1 week after the second Shingrix^®^ dose; * 2: 12 weeks ± 2 weeks after the second Shingrix^®^ dose; * 3: Blood tests include white blood cell count, red blood cell count, haemoglobin, platelet count, albumin, aspartate aminotransferase (AST), alanine aminotransferase (ALT), creatinine, blood urea nitrogen (BUN), CRP, and rheumatoid factor (RF); * 4 Urine test results include urine protein and occult blood; * 5 Immunogenicity evaluation includes anti-gE antibody, gE-specific CD4+ T-cells, and VZV-specific antibodies.

**Table 2 jcm-13-07321-t002:** Type of report.

			Regional Bureau of Health and Welfare	Accredited Clinical Research Review Board	
Type of Report			Regular Report	On-Time Report	Regular Report
Pharmaceuticals	Known	Death	〇	15 days	〇
		Serious condition other than death	〇	15 days	〇
		Non-serious	〇	―	〇
	Unknown	Death	〇	15 days	〇
		Serious condition other than death	〇	30 days	〇
		Non-serious	〇	―	〇
Infection	Known	Death/Serious	〇	15 days	〇
		Non-serious	〇	15 days	〇
	Unknown	Death/Serious	〇	15 days	〇
		Non-serious	〇	―	〇

〇 means required, and ― means not required.

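### In Table 2 the two deadlines that depend on predictability give unknown events slower on-time reporting than known ones, with no reason stated

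*Protocol article*

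**What the plan says.** Section 8.3.4(2) of the protocol article sorts events by predictability. "Events that cannot be predicted from the package insert" and the accompanying precautions are unknown; "those that are listed and can be predicted are categorized as" known.

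Section 8.3.5 makes the reporting table the source of the deadlines. It covers any matter that "requires reporting within the time limit listed in the table below", has the principal investigator report it to the hospital administrator and the review board, and cites Table 2.

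Table 2 ("Type of report") crosses pharmaceuticals and infection with known and unknown and with the gravity of the event. It has one column for on-time reports to the review board, and regular-report columns for the Regional Bureau and the board. Its legend reads "〇 means required, and ― means not required". The row "Serious condition other than death" appears twice under pharmaceuticals: 15 days in the Known block and 30 days in the Unknown block.

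Section 8.3.6 item (2) opens "If the illness is subject to reporting within the deadlines listed in Table 1", and items (2) and (3) of 8.3.7 also refer to Table 1 for reporting periods. Table 1 is the participant timeline.

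**The concern.** The distinction between expected and unexpected events is ordinarily drawn so that the unexpected ones reach the oversight body at least as quickly. Here, wherever the distinction changes a deadline, it works the other way.

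If the table is used as printed, a serious, non-fatal drug or vaccine event that the product information does not foresee may reach the review board later than a foreseen one. An unforeseen non-serious infection would wait for the regular report. Participants take methotrexate, upadacitinib or both, and all receive an adjuvanted vaccine, so timely notice of unforeseen events matters. What is at stake is safety oversight, not the estimation of any endpoint.

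**Working it through.** No statistical formula applies. The check compares each Known row of Table 2 with its Unknown counterpart, using the definitions in 8.3.4(2).

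On-time report to the review board:

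| Block | Event | Known | Unknown | Comparison |
|---|---|---|---|---|
| Pharmaceuticals | Death | 15 days | 15 days | same |
| Pharmaceuticals | Serious, not fatal | 15 days | 30 days | Unknown later |
| Pharmaceuticals | Non-serious | none | none | same |
| Infection | Death or serious | 15 days | 15 days | same |
| Infection | Non-serious | 15 days | none | Unknown has no on-time report |

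1. **Count.** There are 5 matched pairs: 3 are identical and 5 − 3 = 2 differ.
2. **Direction.** In both pairs that differ, the Unknown row is the slower one or the one without an on-time report.
3. **Size.** For serious non-fatal pharmaceutical events the difference is 30 − 15 = 15 days, a ratio of 30 / 15 = 2. This is the only 30-day entry in the table. For non-serious infections the contrast is a 15-day report against none.
4. **Regular reports.** Both regular-report columns are marked as required in every row, including unknown non-serious infections. Those events are therefore still reported, but not on the on-time track.
5. **Effect of exchanging the labels.** Pharmaceuticals, serious non-fatal would become Known 30 and Unknown 15 days. Infection, non-serious would become Known none and Unknown 15 days. Both asymmetries would reverse. The other three pairs would not change, but that follows from their being identical and is no extra evidence for an exchange.
6. **Extraction.** Each row has its full set of cells, the row labels repeat in regular order and the legend is intact. A table broken in conversion from PDF is an unlikely cause.
7. **Cross-references.** Section 8.3.5 cites Table 2 correctly. Section 8.3.6 item (2) and 8.3.7 items (2) and (3) cite Table 1, which holds visits and assessments and no reporting deadlines.

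**The case against.** The strongest reply is that nothing in the document contradicts Table 2. Section 8.3.4(2) only defines the two categories; it gives no purpose for them and does not say that unknown events must be reported sooner. No other section gives a competing deadline, and the regulation is not reproduced. The direction therefore looks wrong by the general logic of expedited reporting, not by the protocol's own words. This stands, and it limits the conclusion to an unexplained asymmetry that needs checking.

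A second reply is that the article condenses a full protocol that is not shown. The slip may exist only in the published table, and staff may be working from a correct one. This also stands: harm to actual reporting cannot be assumed, and any look back at past reports must depend on what the approved protocol says. It does not excuse the article's table, which is printed in full and which 8.3.5 names as the source of the time limits.

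A reader might infer more in three ways, none of which the documents support:

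- **That unpredicted events may go unreported.** Regular reports are required in every row.
- **That all unknown serious events have a longer deadline.** Deaths, and fatal or serious infections, have 15 days in both blocks.
- **That vaccine-related RA flares or immune-mediated disease would be delayed.** The article already anticipates these. Whether they count as unknown depends on the package insert and interview form, which are not shown; if they are listed there, they fall under Known.

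The wrong table number is minor. Section 8.3.5 gives the right one just before, and Table 1 is plainly a visit schedule.

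**Conclusion.** The point holds in a limited form. In the only two of five pairs where predictability changes the on-time deadline, Table 2 is slower for the unpredicted event (30 against 15 days, serious non-fatal pharmaceutical events) or requires no on-time report for it (against 15 days, non-serious infections). The article gives no reason.

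The cells themselves can be read with high confidence. That they are wrong rests on an assumption from general practice: an unexpected event should not be reported more slowly than the same kind of expected event. An exchange of labels is the simplest explanation, since one slip accounts for both differences. It remains an inference, because the intended deadlines cannot be confirmed without the regulation or the full protocol. Whether any report was actually late is unknown.

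The table should be corrected because it governs safety reporting in a trial listed as recruiting. Endpoints, sample size and analysis are not affected. The Table 1 references are a clerical error that would not merit a point on their own.

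**What to change.** 1. Check the two row pairs in Table 2 against the full approved protocol and the governing regulation, and correct them to agree. Exchanging the Known and Unknown labels would resolve both, but the check should decide. If the printed deadlines prove to be intended, state the reason in 8.3.5.
2. If the approved protocol carries the same table, amend it, notify the investigators and the person in charge of monitoring, and re-check the timing of reports already made under it. If the slip is only in the article, a published correction is enough.
3. Change Table 1 to Table 2 in 8.3.6 item (2) and in 8.3.7 items (2) and (3). Table 2 marks regular reports as required but shows no interval for them, so 8.3.7 should also say where that interval is given.

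The cost is a comparison with two source documents, a table correction and, if needed, a short notice to staff. The re-check adds work only if the approved protocol has the same table. No data collection or analysis changes.

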## Data Availability

The dataset used and analyzed in the current study are available from the corresponding author upon reasonable request.

## Abbreviations

AST	aspartate aminotransferase
ALT	alanine aminotransferase
BUN	blood urea nitrogen
CDAI	clinical disease activity index
CRP	C-reactive protein
DAS	disease activity score
ESR	erythrocyte sedimentation rate
gE	glycoprotein E
JAK	Janus kinase
jRCT	Japan Registry of Clinical Trials
RA	rheumatoid arthritis
SDAI	simplified disease activity index
VZV	varicella-zoster virus
